### Usual care

At both recruitment centres, usual physiotherapy after discharge following TKR surgery comprises information and advice on knee-specific and functional exercise. Referral for outpatient physiotherapy is on a needs-only basis when deemed appropriate by a member of the clinical care team. Prior to hospital discharge, patients are assessed on an individual basis by the inpatient physiotherapy team at each centre, and patients with poor range of motion or muscular weakness are referred for outpatient community-based physiotherapy. This referral is at the discretion of the hospital’s physiotherapy or orthopaedic team. General practitioners (GPs) and consultants can also refer patients for outpatient physiotherapy as appropriate. Use of physiotherapy services by participants in both trial arms will be recorded in the trial questionnaires.

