Classes will be held at set weekly times in an outpatient gymnasium at a large NHS hospital and up to a maximum of 12 patients can attend a class. Classes will be supervised by a physiotherapist and physiotherapy technician/assistant, and will run on a rolling system so that new patients can join the classes each week as other patients finish the class. Participants will be reimbursed travel costs that are incurred for their travel to attend classes. Before attending the physiotherapy classes, participants will be asked to complete an Activity Goal Form which involves identifying two functional goals that they would like to achieve. In their first class, each participant will have a discussion with the physiotherapist about these goals to develop two individualised exercises which they begin in their second class. Participants will also be given an exercise booklet in which they record details about their weekly progress in the class.

Each class will involve a short warm up, after which patients follow a simple exercise circuit. The 5-min warm up involves participants mobilising around the gym circuit at a steady pace. This is interspersed with gentle upper limb and lower limb movements including shoulder circumduction, elbow flexion and extension, hip and knee flexion, and ankle circumduction exercises, as each participant is able. The exercise circuit involves 12 exercise stations, including two stations dedicated to individualised exercises. An overview of the exercises stations is provided in Table 1. Four minutes is allocated to each station to provide patients with sufficient time to carry out the exercises at their own pace. The exercises are designed to increase lower limb strength, balance, function and confidence using specific and task-related activities. A selection of graded exercises is provided at each station to enable the patients to exercise at a level suitable to their ability. During weeks 2–6, the exercises are progressed on an individual basis through discussion with the physiotherapists.

**Table 1 Tab1:** Brief description of exercises at each station within the physiotherapy class

Station and exercise	Description	Task

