### Primary outcome

The primary outcome is the Lower Extremity Functional Scale (LEFS) [26] at 12 months post-operative. The LEFS is a validated 20-item questionnaire which assesses lower limb function and difficulty in performing everyday tasks. The LEFS has been recommended as the outcome measure of choice to measure function in patients with knee OA and those undergoing joint replacement because of its good psychometric properties and minimal floor and ceiling effects [38–40].

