### Sample size

The minimal clinically important difference (MCID) for the LEFS is 9 scale points [26]. In our feasibility study, we observed a pooled standard deviation (SD) of 18.4 and a rate of missing LEFS score of 9 % in the intervention group and 35 % in the usual-care group at 6 months post-operative. For the purposes of the sample size calculation we assumed a similar SD for the LEFS at 12 months post-operative, due to the lack of relevant published data. To account for the uncertainty induced by estimating parameters from a small feasibility study, we adjusted the assessed sample by an inflation factor of 1.12^2^, a value derived from the 80 % upper confidence limit of the SD estimate [46]. We also accounted for a missing data rate of 35 %, although we are implementing additional measures to improve LEFS completion rates (e.g. completion of the primary outcome measure over the telephone with non-responders). Therefore, a sample of 256 patients will allow us to detect a MCID (9 points) in the LEFS between trial arms at 12 months post-operative, assuming a power of 80 %, a two-sided 5 % significance level and accounting for up to 35 % missing data and an ‘inflation factor’ of 1.12^2^.

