The analyses will be conducted on an intention-to-treat basis with and without imputation of missing primary outcome data. A multiple imputation (MI) by chained equations under a missing at random framework stratified by randomization arm will be used [47]. These imputed results will be contrasted with other imputation strategies as discussed by White and colleagues [48]. The same modelling strategy will be used to investigate the intervention effect on the KOOS, HADS and patient satisfaction. A sensitivity analysis will investigate the intervention effect using a per-protocol analysis. Information clustering at the recruitment centre level will be addressed using a fixed-effect indicator and clustering of outcomes by surgeon will be investigated and modelled if required. We will also compare the mean/median primary outcome by physiotherapist for patients receiving the intervention and any significant differences will be used to conduct exploratory sub-group analyses. Given the differences in outcomes after TKR for men and women [49], exploratory analysis will be undertaken to investigate the impact of gender.

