## Discussion

This project is a fully powered RCT to evaluate the long-term clinical effectiveness and cost-effectiveness of a novel group-based outpatient physiotherapy intervention following TKR in addition to usual care. The trial includes patients with all levels of functional aspirations, and emphasises the concept of participation in valued activities as a basis for effective and appropriate rehabilitation goals. Our approach aims to both improve function for those patients who may otherwise have unfavourable outcomes, and assist patients who are recovering well to achieve more demanding goals.

A strength of this trial is that the design of the intervention and trial were informed by prior feasibility work [25]. In particular, the feasibility work highlighted the importance of complementing the collection of outcome measures by postal questionnaire with telephone calls to maximise completion rates. This has previously been shown to be an effective strategy with a similar patient population [56], although with the increasing uptake of technology, online questionnaires may be a useful alternative data collection method for future trials. Another strength of this trial is the 12-month follow-up period, which will allow assessment of the long-term impact of physiotherapy on patient outcomes and resource use. However, in addition to patient-reported outcome measures, the trial may have benefitted from the inclusion of more objective measures of function, such as muscle strength or gait analysis, as these capture different dimensions of function [57]. Another limitation of the trial which warrants acknowledgement is the lack of blinding, because of the group-based nature of the physiotherapy intervention. Blinding in trials of physiotherapy is often challenging and only a quarter of physiotherapy trials are blinded [58]. There is a risk that lack of blinding will introduce bias as outcome data will be self-reported by participants who will know which treatment they have been allocated to. A recent meta-epidemiology study found that lack of blinding in physiotherapy trials can lead to an underestimation of the treatment effects compared to trials with blinding, although this was not statistically significant [58]. In addition, while the trial is powered for our primary analysis, other analyses are purely exploratory in nature and will be interpreted as such.

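### Sub-group analyses by physiotherapist are triggered by a significance test on the primary outcome itself, so physiotherapist differences reported after the trigger are exaggerated (minor; the primary analysis is unaffected)

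*Protocol article*

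**What the plan says.** The Statistical analysis section sets a two-step rule: "We will also compare the mean/median primary outcome by physiotherapist for patients receiving the intervention and any significant differences will be used to conduct exploratory" analyses of sub-groups. Step one is a comparison within one arm, and step two depends on its result.

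The outcome in step one is the trial's own endpoint: "The primary outcome is the Lower Extremity Functional Scale (LEFS) [26] at 12 months post-operative" (Primary outcome section).

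A class physiotherapist exists only for patients who attend the classes: "Classes will be supervised by a physiotherapist and physiotherapy technician/assistant, and will run on a rolling system" (Intervention section). Usual care has no such grouping: "Referral for outpatient physiotherapy is on a needs-only basis when deemed appropriate by a member of the clinical care team" (Usual care section).

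The Discussion adds that, apart from the powered primary analysis, "other analyses are purely exploratory in nature and will be interpreted as such".

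The article does not give the number of physiotherapists, their loads, the test to be used, or the form of the sub-group analysis.

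**The concern.** Two features of the written rule are weak.

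- **Selection on the outcome.** Physiotherapist groups are examined further only if their mean LEFS values were seen to differ significantly. Any LEFS difference then reported for those groups is conditional on having been large, so on average it overstates the truth.
- **No randomised counterpart.** Class physiotherapist is determined after randomisation and only in the intervention arm. A treatment effect by physiotherapist would need to know which usual-care patients would have been taught by whom, and the design does not provide that. The gender analysis in the same paragraph is different: gender is a baseline factor present in both arms, it is justified in advance, and it does not depend on a p-value.

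What is at stake is limited: an apparent difference between staff, comparable in size to the trial's MCID, could appear in a report intended to inform service provision when it is largely or wholly noise.

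**Working it through.** **Inputs from the protocol article.** SD 18.4, inflation factor 1.12², MCID 9 points, 80% power, two-sided 5%, 35% missing (Sample size); 1:1 allocation (Randomisation); 128 per arm (Abstract).

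**Assumed, because not stated.** 2, 3 or 4 physiotherapists with equal loads; a one-way F-test at 5% as the trigger; normal outcomes.

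**1. Reproduce the stated sample size.**
- Evaluable per arm: n = 2 × [18.4 × 1.12 × (1.960 + 0.842) / 9]² = 82.3, rounded up to 83.
- Randomised per arm: 83 / 0.65 = 127.7, rounded up to 128. Total 256, as stated.
- The intervention arm therefore has between 83 (35% missing) and 128 (none missing) patients with LEFS.

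**2. Closed-form check with two physiotherapists and no true difference.**
- SE of the difference between two half-arms = 18.4 × √(4/N), which is 4.04 for N = 83 and 3.25 for N = 128.
- Mean absolute gap with no trigger = SE × √(2/π): 3.2 and 2.6 points.
- Mean absolute gap given two-sided significance at 5% = SE × 2φ(1.96)/0.05 = SE × 2.34: 9.4 and 7.6 points.

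With two physiotherapists the trigger thus inflates the reported gap about threefold (2.34 / 0.798 = 2.9).

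**3. Simulation with no treatment effect and no physiotherapist effect** (60,000 trials per row, SD 18.4). Gaps are best minus worst physiotherapist mean, in LEFS points.

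| Patients per arm | Physiotherapists | Trigger fires | Mean gap, all trials | Mean gap, trigger fired |
|---|---|---|---|---|
| 83 | 2 | 5.0% | 3.2 | 9.4 |
| 83 | 3 | 5.0% | 5.9 | 13.1 |
| 83 | 4 | 4.9% | 8.3 | 16.1 |
| 128 | 2 | 5.0% | 2.6 | 7.5 |
| 128 | 3 | 5.0% | 4.8 | 10.5 |
| 128 | 4 | 4.9% | 6.7 | 13.1 |

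The first row of each block agrees with step 2.

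**4. If physiotherapists truly differ.** Assume a true between-physiotherapist SD of 4.1 points, so the ICC is 4.1² / (4.1² + 18.4²) = 0.047. The trigger then fires in about 26–38% of trials. Given that it fires, the observed best-to-worst gap averages about 10–18 points, while the true gap between the same two physiotherapists averages about 7.6–9.4. A real difference makes the rule fire more often, and its size is still overstated.

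**5. If the sub-groups were also compared with usual care, which the protocol does not specify.** In the null simulation, a t-test of each physiotherapist's patients against the whole usual-care arm gives at least one p < 0.05 in about 46–79% of trials in which the trigger fired. Multiplied by the 5% firing rate, that is about 2–4% of all null trials. The same tests run with no trigger would give at least one p < 0.05 in about 9–18% of trials.

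**The case against.** The strongest reply has four parts.

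- **The protocol does not say the sub-groups will be set against usual care.** This stands. A reader might infer that the report will contain a physiotherapist sub-group that appears to beat usual care. The text does not support that: the comparison is introduced for intervention recipients, and a description within that arm is an equally natural reading. Step 5 is therefore conditional. The exaggeration in steps 2 to 4 concerns the within-arm gap and does not depend on a usual-care comparison.
- **The trigger rarely fires by chance.** This also stands: it fires in about 5% of trials if physiotherapists do not differ. It would be wrong to say that the rule will show spurious effects, or to set 46–79% beside a nominal 5%. The first is a conditional rate over several tests and the second an unconditional rate for one test. Taken over all null trials, the trigger lowers the chance of a nominally significant sub-group, to about 2–4%. What it harms is the size of the estimate once it fires.
- **The analyses are labelled exploratory.** The label limits how the result may be interpreted, and it protects the primary conclusion. It does not remove the upward bias in the estimate that gets reported.
- **The form of an exploratory analysis belongs in the analysis plan.** The form may, and its absence is not the criticism. The significance trigger is stated in the article, and that is what is questioned.

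If one physiotherapist takes every class, the point falls away; the sentence itself presupposes more than one.

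**Conclusion.** The point holds as a minor one. The article makes sub-group analyses by physiotherapist depend on a significant difference in the outcome that those analyses would then describe. When the trigger fires with no true difference, the best-to-worst gap averages about 7.5–16 points, against 2.6–8.3 without it, and can exceed the 9-point MCID. With a true difference, the gap is still overstated. Independently of this, no randomised treatment-by-physiotherapist comparison exists, because the factor arises after randomisation in one arm only.

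These figures rest on 2 to 4 physiotherapists with equal loads, an F-test at 5%, SD 18.4 and 83–128 patients per arm; the number of physiotherapists and the test are assumptions. The primary analysis, the sample size and the main conclusion are not affected.

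**What to change.** Amend the one sentence in the Statistical analysis section, and the matching text in the analysis plan:

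- Delete the significance trigger.
- Report 12-month LEFS for every physiotherapist within the intervention arm, with confidence intervals, whatever the p-value. If there are enough physiotherapists, add shrunken means or a between-physiotherapist variance component with its interval. With only two to four, a variance component would be very imprecise, and the descriptive means should carry the report.
- State that no physiotherapist-specific treatment effect against usual care will be estimated.

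The cost is a wording change and the loss of one exploratory sub-group result. The data are those the planned comparison already needs, and no sample-size figure changes.

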### Statistical analysis

Analysis will follow a Statistical and Health Economics Analysis Plan which will have been approved a priori by the Trial Steering Committee. Data presentation and analysis will be in accordance with Consolidated Standards of Reporting Trials (CONSORT) guidelines. Baseline characteristics will be reported by trial arm using percentages, means (SDs) or medians (interquartile ranges) as appropriate. The repeated measures of primary and secondary outcomes will be plotted by trial arm.

The main analysis will consist of a linear mixed regression (with random intercept for patient to control for the repeated follow-ups) with an interaction between the intervention effect and the assessment time adjusted for pre-operative function and recruitment centre. The use of these interactions terms will allow us to assess and single out the specific effect of the intervention on LEFS at 12 months post-operative, and then identify the intervention-specific effects at 3 and 6 months post-operative (secondary outcomes). The regression will then be adjusted for imbalanced individual characteristics between arms at baseline. Other types of generalised linear mixed models will be considered if the former approach is not fitting the distribution of the residuals of the regressed (transformed) primary or secondary outcomes. The model will finally be adjusted for type of additional physiotherapy treatment received (physiotherapy received that is not delivered as part of the intervention). The trial is not powered for such adjustments and it will only inform us on their potential impact on the intervention effect.

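### Only intervention patients share physiotherapist-led classes, yet the sample size and main model treat all patients as independent, and the stated physiotherapist rule does not correct the standard error

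*Protocol article*

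**What the plan says.** Under Intervention, classes are supervised by a physiotherapist with an assistant, entry is rolling, and "up to a maximum of 12 patients can attend a class". The physiotherapist also develops each patient's individualised exercises, progresses them and writes the home plan. Under Usual care there is no trial class and no trial physiotherapist.

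Under Sample size, "a sample of 256 patients will allow us to detect a MCID (9 points) in the LEFS between trial arms at 12 months post-operative". The ingredients are an MCID of 9, a feasibility SD of 18.4, an inflation for uncertainty in that SD, and 35% missing data. No ICC or design effect appears.

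Under Statistical analysis, the main model is a "linear mixed regression (with random intercept for patient to control for the repeated follow-ups"), adjusted for pre-operative function and centre. Centre is a fixed effect, and surgeon clustering is to be modelled if needed. Physiotherapist is handled differently: LEFS means or medians are compared between physiotherapists among intervention patients, and "any significant differences will be used to conduct exploratory sub-group analyses". Class is not mentioned as a source of clustering.

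**The concern.** Group delivery in one arm makes this a partially nested design. Patients taught by the same physiotherapist, or exercising together, may end up more alike than patients in different groups. Any such correlation inflates the variance of the intervention-arm mean and leaves the usual-care mean untouched. A model that omits it gives a standard error that is too small.

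The stated step does not deal with this. Whatever the comparison between physiotherapists shows, the main model stays the same. A significance screen across few physiotherapists would have little power to detect a small ICC. Usual-care patients cannot be assigned to a trial physiotherapist, so a sub-group defined by physiotherapist has no randomised comparator of its own. Surgeon, by contrast, is offered a model term, although surgery precedes randomisation and each surgeon's patients can therefore fall in both arms.

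At stake are the width of the 12-month confidence interval, the 5% error rate, and the claim of 80% power.

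**Working it through.** **Inputs from the Sample size section.** "The minimal clinically important difference (MCID) for the LEFS is 9 scale points"; "we observed a pooled standard deviation (SD) of 18.4"; "we adjusted the assessed sample by an inflation factor of 1.12^2"; "assuming a power of 80 %, a two-sided 5 % significance level"; 35% missing; 256 patients, 128 per arm.

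**Reproducing 256.** With independent patients, n per arm = 2(1.96 + 0.842)² × 18.4² / 9² = 65.6. Multiplying by 1.12² = 1.2544 gives 82.3, rounded up to 83. Dividing by 0.65 gives 127.7, rounded up to 128, and 2 × 128 = 256. The match is exact, so the figure holds no allowance for clustering.

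**Baseline case.** Planning SD = 18.4 × 1.12 = 20.6. With 83 analysed per arm, SE = 20.6 × √(2/83) = 3.20. Power = Φ(9/3.20 − 1.96) = 80.3%.

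**Adding clustering in the intervention arm only.** The documents give neither the ICC nor the number of patients per cluster (m), so both are assumptions. The upper m of 12 is the class maximum.
- Design effect: DE = 1 + (m − 1) × ICC
- SE = 20.6 × √(1/83 + DE/83)
- Power = Φ(9/SE − 1.96)
- Type I error if clustering is ignored = 2 × [1 − Φ(1.96 × 3.20/SE)]

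| m | ICC | DE | SE | Power | Type I error if ignored |
|---|---|---|---|---|---|
| 6 | 0.01 | 1.05 | 3.24 | 79% | 5.3% |
| 6 | 0.02 | 1.10 | 3.28 | 78% | 5.6% |
| 6 | 0.05 | 1.25 | 3.39 | 76% | 6.5% |
| 12 | 0.01 | 1.11 | 3.29 | 78% | 5.6% |
| 12 | 0.02 | 1.22 | 3.37 | 76% | 6.3% |
| 12 | 0.05 | 1.55 | 3.61 | 70% | 8.3% |

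In the last row the true SE is 3.61/3.20 = 1.13 times the one the model reports.

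**Possible slack in power.**
- If the SD is 18.4 rather than 20.6, power is 88% without clustering and just under 80% at m = 12, ICC 0.05.
- If missing data follow the feasibility study (9% intervention, 35% usual care), about 116 and 83 are analysed. At SD 20.6, power is 86% without clustering and 78% at m = 12, ICC 0.05.
- Type I error in that same cell stays at 8.3% in the first case and 7.7% in the second.

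**The case against.** **Size.** The size rests on assumed inputs. At ICC 0.01 with 6 per cluster the loss is about one point of power and 0.3 points of type I error. The documents support *could be too narrow*, not *is*.

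**Slack.** The SD inflation and the 35% allowance may leave room, as may adjustment for pre-operative function, which the sample size does not credit. This stands for power under moderate clustering. However, the two allowances were made for other uncertainties, and no amount of slack repairs an understated standard error.

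**Cluster definition.** Rolling entry means class membership changes weekly, so class has no natural boundary. This stands, and the analysis must define its cluster. It does not make the patients independent.

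**Exploratory label.** The physiotherapist comparison is exploratory and is not presented as a variance correction. That is fair. It is nevertheless the only handling of physiotherapist in the article, and it leaves the primary analysis unprotected.

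**Unseen analysis plan.** The separate analysis plan might add a term. But the article states a specific approach to physiotherapist, so the point concerns what is stated, not what is left out.

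**Stronger readings to avoid.** A reader might suppose that a handful of physiotherapists treat everyone. At three physiotherapists (about 28 patients each) and ICC 0.05, the same formulas give about 59% power and 13% type I error. The documents give no number of physiotherapists, so those figures cannot be attributed to this trial. Nor does it follow that a physiotherapist random effect should replace the main model. With three clusters, small-sample degrees of freedom would be about 4 to 6, and power about 61% to 39% over ICC 0.01 to 0.05. That cost is heavy, and the variance would be poorly estimated.

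**Conclusion.** The point holds in a limited form. Clustering arises in the intervention arm only, 256 assumes there is none, and the stated physiotherapist step cannot correct the treatment-effect standard error. Under the planning inputs, with clusters of 6 to 12 and ICC 0.01 to 0.05, power is about 79% to 70% and type I error about 5.3% to 8.3%. These are illustrations under assumed ICCs and cluster sizes, not estimates for this trial. The documents do not show that the interval will be too narrow or that the trial is underpowered. They show that the protection claimed at 5% and 80% depends on an unstated assumption of no clustering.

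**What to change.** Replace the rule of comparing physiotherapists and then forming sub-groups with a pre-specified, partially nested sensitivity analysis of the primary LEFS model:
- a random effect in the intervention arm only, for physiotherapist or for a defined class period (for example a start-date block, given rolling entry);
- each usual-care patient as their own cluster;
- residual variance allowed to differ by arm.

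Report the ICC. Beside the 80% power, state that it assumes no clustering, and give the power for ICC 0.01 to 0.05.

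Cost: physiotherapist and class start date must be in the dataset; physiotherapists already complete Case Report Forms. The sensitivity interval will be wider, and much wider if there are very few physiotherapists. The stated power becomes less favourable. The main model can stay as it is, and no extra patients are needed.
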